## Method and design

### Aim of the study

The overall aim of the study is to evaluate the efficacy of individualized lifestyle intervention compared to the usual care in PCOS women who wish to conceive. We hypothesized that individualized lifestyle intervention improves fertility outcomes in PCOS women who wish to conceive when compared to the usual care. To test the hypothesis, we plan to randomize PCOS women into two groups: group A will receive the intervention which will consist of individualized advice on diet and physical exercise along with a telephonic reminder system and follow-up visits, and group B (control) will receive one-time advice on diet and physical exercise. Both groups will receive up to three cycles of ovulation induction with letrozole after 3 months of randomization during the 6-month treatment period.

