### Sequence generation and allocation concealment

Once eligibility is confirmed, web-based randomization will be initiated in the presence of the trial staff. The randomization will be done using PHP as the frontend and MySQL as the backend database. Block randomization stratified for the site and BMI (≥ 23–27 kg/m^2^ and > 27 to ≤ 35 kg/m^2^) will be performed. The randomization will be done in a 1:1 ratio to the intervention or the control arm. The trial staff from each site will enter the participant information following which a randomization number will generated and assigned if they fulfil the eligibility criteria. The random number and the allotted arm details will be provided to the trial staff by an authorized person in each site. The allocation will be concealed until the point of randomization. The allotted intervention will be informed to the clinical team as well as the trial staff, and the trial number will be noted.

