### Control

Usual care, which is the medical advice/fertility treatment as per unit protocol for those seeking fertility treatment and one time referral to the dietician for dietary advice and exercise by the physiotherapist in the fertility clinic. There will be no planned follow-up for compliance for the lifestyle intervention in the control arm. The control also will receive the fertility treatment after 3 months following randomization if they do not conceive as per unit protocol. The participant will be reviewed after 6 months to measure the anthropometric and reproductive outcomes at the department of reproductive medicine and surgery/gynaecology outpatient clinic. This visit will be combined with any medical treatment-related appointment to avoid multiple visits to the hospital. As mentioned, the participant in the control arm also will receive medical treatment as per unit protocol 3 months post-randomization if she does not conceive.

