### Medical treatment 3 months post-randomization for intervention and control arm

These will be as per standard infertility guidelines starting with letrozole. Ovarian induction may be followed with timed intercourse or IUI (combined male factors such as sexual dysfunction) as per the participant’s profile. The treatment will be given for up to 3 cycles depending on the unit policy, while the lifestyle intervention follow-up will continue in the interventional arm over the next 3 months, to be completed for 6 months.

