#### Week 13– (session 2) (only for the intervention arm)

In person to check compliance for diet and physical exercise, check weight and anthropometric parameters and as the pregnancy status of the participants. An ultrasound will be performed before initiating ovulation induction.

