#### Week 26– (session 3) (for both the intervention and control arms)

In person check anthropometry and blood tests (hormones and metabolic parameters) and TVS. The following blood tests will be repeated at 6 months: AMH, serum testosterone, SHBG, serum insulin (fasting and 2 h post-meal), blood sugar (fasting and 2 h post-prandial), fasting lipid profile, glycosylated haemoglobin (HbA1C), SGPT, uric acid and serum adiponectin.

Compliance with dietary intake and physical exercise will be assessed for participants in the intervention and control arms using 24 h diet recall and GPAQ tool.

Medical treatment for infertility can be commenced after 12 weeks on post-randomization in case the participant does not conceive. The lifestyle intervention shall stop at 6 months when a final follow-up on anthropometry, metabolic, hormonal and ultrasound will be done in women from both arms. For those who conceive within 6 months post-randomization, the follow-up will extend until delivery/end of pregnancy for recording obstetrics and neonatal outcomes.

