We plan to adjust the results for the following covariates: (i) number of letrozole cycles. Logistic regression analysis will be used to adjust the covariates effectively the adjusted effect size will be presented as an odds ratio (95% CI) for binary outcomes. All the analyses will be performed using STATA/IC 16.0.

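### The only covariate named for the adjusted analysis, the number of letrozole cycles, is fixed after randomisation and driven largely by conception, so the cycle-adjusted odds ratio for live birth does not estimate the effect of the intervention

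*Protocol article*

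**What the plan says.** The adjustment plan, at the end of the Statical analysis section, names one covariate: "We plan to adjust the results for the following covariates: (i) number of letrozole cycles". The model follows directly: "Logistic regression analysis will be used to adjust the covariates effectively the adjusted effect size will be presented as an odds ratio (95% CI"). This model is meant for yes/no endpoints, and live birth, the primary outcome, is one, counted per woman.

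The treatment schedule settles what the count measures.

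- Aim of the study: "Both groups will receive up to three cycles of ovulation induction with letrozole after 3 months of randomization during the 6-month treatment period".
- Control: "The control also will receive the fertility treatment after 3 months following randomization if they do not conceive as per unit protocol".
- Week 26 (session 3): "Medical treatment for infertility can be commenced after 12 weeks on post-randomization in case the participant does not conceive".
- Medical treatment 3 months post-randomization: "The treatment will be given for up to 3 cycles depending on the unit policy".

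The Statical analysis section also plans an unadjusted intention-to-treat z-test for proportions, with the risk difference, its 95% CI and the number needed to treat. Dropouts without outcome information count as no live birth. On randomisation, the article says: "Block randomization stratified for the site and BMI".

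**The concern.** A covariate in the analysis of a randomised comparison should be fixed before randomisation, or at least be something that treatment cannot change. This one fails on both counts. A woman who conceives in the first three months has 0 cycles. One who conceives on letrozole has no reason for another cycle. One who never conceives can reach 3. The count is largely a record of the timing of conception, and conception is a necessary step to live birth. The trial's hypothesis is that lifestyle advice improves fertility, and time to pregnancy is a secondary outcome, so the plan itself expects the intervention to shift this variable.

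Conditioning on the count takes out whatever benefit arises through conception before letrozole. It also compares women who share a cycle count but reached it by different routes. At stake is a report in which a z-test showing benefit stands beside an adjusted odds ratio near 1, or in which equal live birth rates stand beside an adjusted odds ratio away from 1, with nothing in the article saying which result governs.

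**Working it through.** **Inputs from the article.** Control live birth 30%, difference 10 points, alpha 0.05, power 90%, attrition 20%, 600 women per arm, up to 3 cycles, dropouts counted as no live birth.

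**The plan's own figure.** (1.960 + 1.282)² × (0.30×0.70 + 0.40×0.60) / 0.10² = 472.8, so 473 per arm and 946 in total. Then 946 / 0.80 = 1182.5, so 1183. Both match the article (two-sided, unpooled variance). The sample size rests on the unadjusted comparison and is not in question. The matching crude odds ratio is (0.40/0.60) / (0.30/0.70) = 1.56, with 95% CI 1.22 to 1.98 at 600 per arm.

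**Assumptions that are not in the article.** Let *a* be the probability of a conception leading to live birth before letrozole, and *b* the constant probability per cycle. Cycles stop at conception. Live birth is then a + (1 − a)[1 − (1 − b)³]. Controls: a = 0.05, and b = 1 − (0.70/0.95)^(1/3) = 0.0968, which gives 30%.

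**No dropout.** Under this model every woman with 0, 1 or 2 cycles has a live birth. Only the 3-cycle group contains both outcomes, so the adjusted odds ratio reduces to the ratio of per-cycle odds, [b₁/(1 − b₁)] / [b₀/(1 − b₀)], with b₀/(1 − b₀) = 0.1072. Linear and categorical coding agree here.

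- All benefit before letrozole: a = 0.186, b unchanged. The ratio is 1.00.
- Mixed: a = 0.10, b = 1 − (0.60/0.90)^(1/3) = 0.1264, odds 0.1447. The ratio is 1.35.
- Per cycle only: a = 0.05, b = 1 − (0.60/0.95)^(1/3) = 0.1420, odds 0.1655. The ratio is 1.54.
- Equal live birth (30% in both arms) but earlier conception in the intervention arm: a = 0.12, b = 1 − (0.70/0.88)^(1/3) = 0.0734, odds 0.0792. The ratio is 0.74.

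**With 20% dropout in each arm, placed at 0 cycles with no live birth.** Live birth becomes 0.8 × 30% = 24% and 0.8 × 40% = 32%, so the crude odds ratio is (0.32/0.68) / (0.24/0.76) = 1.49. Logistic models were fitted to the expected cell counts at 600 per arm.

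| Scenario | Crude, no dropout | Adjusted, no dropout | Crude, 20% dropout | Adjusted, linear | Adjusted, categorical |
|---|---|---|---|---|---|
| All benefit before letrozole | 1.56 | 1.00 | 1.49 | 1.32 | 1.96 |
| Mixed | 1.56 | 1.35 | 1.49 | 1.42 | 1.60 |
| Per cycle only | 1.56 | 1.54 | 1.49 | 1.47 | 1.32 |
| Equal live birth, earlier conception | 1.00 | 0.74 | 1.00 | 0.94 | 1.33 |
| Intervention changes nothing | 1.00 | 1.00 | 1.00 | 1.00 | 1.00 |

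**Sensitivity to the assumptions.** A second set took 10% of control women conceiving before letrozole and 80% of conceptions ending in live birth, with *b* recalibrated so that live birth stayed at 30% versus 40% at each dropout level (crude 1.56 throughout). With all benefit before letrozole, the adjusted odds ratio was 0.84 (linear) or 1.00 (categorical) with no dropout, and 1.29 or 1.75 with 20% dropout. With equal live birth but earlier conception and no dropout, it was 0.66 (95% CI 0.47 to 0.92) linear or 0.81 categorical. With 20% dropout it was 0.94 or 1.20.

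**The case against.** The strongest defence is that the trial's main comparison is untouched. The z-test, the risk difference, the number needed to treat and the sample size do not use the cycle count. A reader might infer from the figures above that the trial's answer on live birth is compromised. The article does not support that: the fault is confined to the adjusted analysis. What remains is that the article speaks of adjusting the results without calling that analysis secondary.

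The second defence is that the size is fragile. This stands. If the benefit arises only per cycle, a linear count barely moves the estimate. With the plan's own 20% attrition the collapse to 1.00 does not occur, and categorical coding can reverse the direction. If the intervention changes neither conception timing nor dropout, there is no bias. No single figure should be quoted as the size of the error.

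Third, it is loose to say that the outcome itself sets the count. Conception, not live birth, ends the cycles, and unit policy and dropout also matter.

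Fourth, the phrase could mean cycles taken before enrolment. Prior cycles appear only as an exclusion limit, the adjustment sentence does not say prior, and the treatment sections use letrozole cycles for trial treatment. This reading is weak.

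A further inference is tempting: that controls will receive fewer cycles because the week-13 visit is headed "session 2) (only for the intervention arm"). The article does not say so. It gives both arms up to three cycles from the same time point, and the one-arm visit mainly concerns compliance and measurements. Unequal access is conjecture, and the point does not need it.

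Finally, the absence of site and BMI from a condensed article's covariate list is not itself a fault. The listing of a post-randomisation variable is.

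**Conclusion.** The point holds for the adjusted analysis. The article specifies a covariate that its own schedule makes post-randomisation and dependent on conception, so the resulting odds ratio does not estimate the effect of individualised lifestyle advice on live birth. This follows from the schedule alone.

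The magnitude does not. With a linear count, adjustment moves an odds ratio of 1.56 to between 1.00 and 1.54 with no dropout, and 1.49 to between 1.32 and 1.47 with 20% dropout. Equal live birth rates can yield about 0.74 with no dropout or 0.94 with 20% dropout. These ranges rest on assumed values for pre-letrozole conception and per-cycle success, and they change with coding and with the proportion of conceptions ending in live birth. The unadjusted intention-to-treat comparison is not open to this objection.

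**What to change.** - Delete the number of letrozole cycles as a covariate.
- If an adjusted odds ratio is reported, adjust only for baseline variables, namely the randomisation strata: site and BMI.
- State that the intention-to-treat comparison without the cycle count is the primary result.
- Report the number of cycles received, by arm, descriptively.

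The cost is a change of wording in the protocol and any analysis plan, best made before outcome data by arm are seen. Sample size, visits and data collection stay as they are.

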### Protocol amendments

The final protocol was approved on 2 April 2023. During the conduct of the trial, if any major protocol amendment is made, we plan to inform the ethics committee of all the sites, the sponsor as well as the TSC.

## Discussion

Lifestyle intervention is considered as the first line of management for treating PCOS women who present with infertility. While earlier studies have shown some improvement in menstrual symptoms, endocrinological parameters and ovulation rate, very few have reported clinically important fertility outcomes, i.e. live birth [11–14]. The current trial is planned to capture all the relevant clinical domains which are important to the PCOS women such as reproductive outcomes, improvement in menstrual symptoms, changes in anthropometric measurements and endocrinological parameters and, finally, the quality-of-life score.

High dropout rates and adherence issues are some of the challenges in trials evaluating lifestyle intervention [10, 26]. The Cochrane review evaluating the lifestyle intervention reported high dropout rates (up to 46%), especially in studies involving longer treatment periods [10]. A systematic review investigated the dropout rates in studies evaluating the lifestyle intervention in overweight and obese infertile women [26]. The review included 15 studies, out of which 10 reported the dropout rate. The median dropout rate was 24% (range 0–31%). The authors could not find any modifiable predictors for dropouts and reported lower weight loss in women who had dropped out of the trial. The current study has calculated the sample size taking into account the possibility of high attrition (20%) that may be encountered during the conduct of the trial. In the currently planned trial, it has been hypothesized that customized lifestyle intervention delivered by the medical staff other than the treating clinician may help in greater adherence and lower dropouts. The study will indirectly help us investigate the impact of such an approach on the attrition rate for the lifestyle intervention.

One of the reasons for planning the current study is the limited applicability of trial findings conducted in other parts of the world, such as Europe and North America due to marked differences in dietary patterns [27]. Furthermore, there are also differences in the level and nature of daily physical activity performed by women from South Asian region versus women from European or North America [28]. Some of the urban areas in South Asia have problems with limited public space and access to sporting facilities. Hence, it is important to customize the lifestyle interventions depending on each individual’s preferences and availability of resources. Moreover, the South Asian phenotype related to obesity is prone to developing complications at a lower body mass index and more resistant to lifestyle intervention [29, 30].

An adequately powered sample size is one of the main strengths of the current study. Involving multiple sites across the different regions of the country will help in the generalizability of the findings. It is hypothesized that the customized lifestyle intervention for PCOS women primarily involving the dietician and physiotherapist and reducing the involvement of medical doctors may help improve compliance. In low-resource settings, the medical doctor is often overburdened and may not be able to deliver such time-consuming interventions in an optimum manner. The intervention, if found to be beneficial, can be replicated in real-world clinical practice, especially in a low-resource setting. One of the limitations of the study is the difficulty in assessing adherence to the given dietary and exercise-related advise. While it is possible to add additional monitoring tools such as electronic gadgets for exercise and measuring diet specific marker or metabolite in blood or urinary sample, we avoided using such tools as it is difficult to replicate such measures in real-world practice, especially in low-resource setting.

Through this protocol, we would like to connect with other investigators who are planning to initiate similar trials or have ongoing projects investigating lifestyle interventions in women with PCOS. We would like to invite the investigators of such projects to join us through a collaborative framework such as prospective meta-analysis or data sharing arrangement plan for future individualized participant metanalysis [31].

The guidelines have always emphasized the lifestyle intervention as the first line of management for PCOS women [9]. However, these recommendations are mostly based on data from smaller trials with limited generalizability. The current trial results could help clarify and provide more robust evidence for advocating an individualized lifestyle intervention in PCOS women who wish to conceive.

## Trial status

The trial will be open for recruitment from 1 May 2023. We expect to complete the recruitment of all the participants by March 2027 and the follow-up by December 2027. The protocol version 1 was approved on 2 April 2023.

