### Primary outcome

The primary outcome for the trial will be the live birth following conception during the intervention period (time frame: 0 to 16 months post-randomization for participants who conceive within 6 months following randomization). A live birth is defined as the delivery of a live foetus after 20 weeks of gestation [23]. The twins and higher births will be considered as a single live birth event. The denominator for primary analysis will be per woman.

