### Secondary outcomes

There will be several secondary outcomes which will measure clinical, endocrinological and quality of life parameters and are listed below:(i)Clinical pregnancy rate (time frame: 0 to 9 months post-randomization for participants who conceive within 6 months following randomization): ultrasound evidence of gestational sac or definitive clinical evidence of pregnancy. An ectopic pregnancy will also be considered a clinical pregnancy [24].(ii)Ongoing pregnancy rate (time frame: 0 to 9 months post-randomization for participants who conceive within 6 months following randomization): a viable intrauterine pregnancy as documented by ultrasound after 12 completed weeks of gestation.(iii)Miscarriage rate (time frame: 0 to 12 months post-randomization for participants who conceive within 6 months following randomization): miscarriage is defined as a spontaneous loss of pregnancy before 20 completed weeks of gestational age [23].(iv)Ectopic pregnancy rate (time frame: 0 to 9 months post-randomization for participants who conceive within 6 months following randomization): ectopic pregnancy is defined as pregnancy outside the uterus as diagnosed by ultrasound, surgically or by histopathology [24].(v)Stillbirth: defined as the death of a foetus prior to the complete expulsion or extraction from its mother after 20 completed weeks of gestational age [23].(vi)Time to pregnancy (time frame: 0 to 8 months post-randomization for participants who conceive within 6 months following randomization): from randomization to the documentation of pregnancy (calculated in days).(vii)Positive pregnancy rate (time frame: 0 to 7 months for participants who conceive within 6 months following randomization): defined as positive urine pregnancy test or serum beta human chorionic gonadotrophin (hCG) > 5 IU/ml.(viii)Mean weight loss (time frame: 6 months post-randomization): difference between baseline and follow-up at 6 months).(ix)Improvement in menstrual regularity (time frame: 6 months post-randomization): (according to the International Federation of Gynecology and Obstetrics (FIGO) 2018 guidelines variation of the cycle to be called regular is 7–9 days depending on age. Age 18–25 years ≤ 9 days; age 26–41 years ≤ 7 days is regular); proportion of women in whom regularization of the menstrual cycle is recorded by a total number of women in whom menstrual regularity is recorded.(x)Differences in anthropometric parameters (time frame: 6 months post-randomization) (waist circumference, hip circumference, neck circumference, waist hip ratio, waist height ratio and wrist circumference) at the end of the trial period.(xi)Improvement in hormonal and metabolic parameters (time frame: 6 months post-randomization) [biochemical markers such as lipid profile and glycaemic parameters, visceral adiposity index (VAI) and lipid accumulation product (LAP)] over the baseline.(xii)Quality of life (PCOS specific) assessment (time frame: 6 months post-randomization) [22].(xiii)Pregnancy-related complications (time frame: 0–17 months post-randomization for participants who conceive within 6 months following randomization) (GDM, PIH, preterm birth): obstetric outcomes—gestational diabetes, hypertensive disorder of pregnancy, preterm delivery (< 37 weeks), very preterm birth (< 32 weeks), low birth weight (< 2500 g) or high birth weight (> 4000 g)

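### The expected end of follow-up, about 9 months after the expected last randomisation, contradicts the 16-month live-birth window, follow-up to delivery and the 17-month complication window

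*Protocol article*

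**What the plan says.** Four statements in the protocol article bear on this.

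- **Trial status.** Recruitment: "The trial will be open for recruitment from 1 May 2023". Completion: "We expect to complete the recruitment of all the participants by March 2027 and the follow-up by December 2027".
- **Primary outcome.** "The primary outcome for the trial will be the live birth following conception during the intervention period", with the time frame "0 to 16 months post-randomization for participants who conceive within 6 months following randomization".
- **Week 26 (session 3).** For women who conceive within 6 months, "the follow-up will extend until delivery/end of pregnancy for recording obstetrics and neonatal outcomes".
- **Secondary outcomes, item (xiii).** "Pregnancy-related complications (time frame: 0–17 months post-randomization", again for conceptions within 6 months.

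No section gives a later date for collecting births, and none explains how a December 2027 end fits these windows.

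**The concern.** The time from last randomisation to last outcome follows from the trial's own definitions. Conception counts up to month 6 and the birth must then be awaited. A 9-month interval covers the 6-month visit with about 3 months to spare, which is too short for most pregnancies in the last women recruited.

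Live birth is the primary outcome, and the Background presents it as what earlier trials lacked. If December 2027 became the date on which data are closed, funding ends or the analysis is run, a share of the primary outcome would be unknown at that point, as would obstetric and neonatal results for the same women. The late recruits are also identifiable in advance, so the gap can be removed at the planning stage.

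**Working it through.** **Inputs from the article.** Recruitment 1 May 2023 to March 2027 (47 months); follow-up to December 2027; 1200 women, 600 per arm; live birth 30% versus 40%; two-group z-test for proportions; alpha 0.05; letrozole from month 3 in both arms.

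**Assumptions not in the article.** Uniform accrual; 38 weeks (266 days, about 8.75 months) from conception to birth; conceptions leading to birth uniform over months 0–6 or, since letrozole starts after month 3, over months 3–6; recruitment to 31 March and follow-up to 31 December 2027.

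**1. The plan's own figure.** Two-sided, unpooled variance: n = (1.960 + 1.282)² × (0.30×0.70 + 0.40×0.60) / 0.10² = 472.8, so 473 per arm. Then 946 / 0.80 = 1182.5, so 1183. Both match the article. The sample size is not in question, and the same variance formula is used for power below.

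**2. Calendar.**
- March 2027 to December 2027: 9 months (8 to 10 depending on the days of the month).
- March 2027 + 16 months = July 2028; + 17 months = August 2028.
- Shortfall: 16 − 9 = 7 months for live birth; 17 − 9 = 8 months for complications.

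**3. Women without the full 16 months.** Accrual is 1200 / 47 = 25.5 per month. The last 7 months of recruitment give 7 × 25.53 = 179 women, or 14.9%. This counts women with a shortened window, not births lost.

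**4. Births after 31 December 2027.** A woman randomised *s* months before recruitment closes has 9 + *s* months of follow-up. Her birth falls after the cut if conception month + 8.75 > 9 + *s*, that is, if conception is later than month 0.25 + *s*.
- *Months 3–6:* every birth is missed for *s* up to 2.75; the share then falls linearly to zero at *s* = 5.75. The total is 2.75 + 3/2 = 4.25 months of accrual, and 4.25 / 47 = 9.0% of births.
- *Months 0–6:* the share is (5.75 − *s*) / 6. The total is 5.75² / 12 = 2.76 months, and 2.76 / 47 = 5.9% of births.
- With a mean rate of 35% there are 420 births, so about 25 (5.9%) to 38 (9.0%) fall after the cut.
- Among March 2027 recruits, about 87% (months 0–6) to 100% (months 3–6) of term births fall after the cut.

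**5. Conditional worst case.** Suppose data close in December 2027 and every one of these pregnancies is scored as no live birth. Power = Φ(difference / √[(p₁q₁ + p₂q₂)/600] − 1.96). The table uses the 9% loss.

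| Scenario, 600 per arm | Rates | z − 1.96 | Power |
|---|---|---|---|
| No dropout, births complete | 30% v 40% | 3.651 − 1.96 | 95.5% |
| No dropout, 9% of births lost | 27.3% v 36.4% | 3.399 − 1.96 | 92.5% |
| 20% dropout as failure, births complete | 24% v 32% | 3.098 − 1.96 | 87.3% |
| 20% dropout as failure, 9% of births lost | 21.8% v 29.1% | 2.904 − 1.96 | 82.7% |

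The absolute difference shrinks from 10 to 9.1 percentage points without dropout. With the 5.9% loss the losses of power are smaller.

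**The case against.** The December 2027 date is an expectation in a status paragraph. It is not called a data cut, a database lock or an analysis date. The rule for conducting the trial is the one under Week 26, which carries follow-up to the end of each pregnancy, and a site that obeys it would record late births whatever the status paragraph says. Sixteen months is also an upper bound: on the 38-week assumption a month-6 conception delivers at about 14.75 months, and early conceptions or preterm births among late recruits could still be seen by December 2027. All of this stands. A reader might infer that births in late recruits cannot be observed; the article supports that only if data really close on that date, and then for most births in the last recruits rather than all births in late recruits.

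A reader might also infer that the missing-outcome rule turns these pregnancies into failures. The rule in the statistical analysis section covers dropouts with no outcome information. The Dropout criteria section defines dropouts by missed 3- and 6-month visits or withdrawn consent, and Table 1 by not attending at 6 months. A woman who attends at 6 months and is pregnant is none of these, so the rule does not clearly reach her.

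The size is modest as well. Without dropout, worst-case power stays above the planned 90%. The fall from 95.5% to 87.3% comes from counting dropouts as failures, which is a separate matter; the date gap adds 4.6 points to it. The cut-off applies to both arms.

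Two rebuttals fail. Reading the stated end as that of the 6-month lifestyle follow-up would place it around September 2027 and leave no date at all for births. And slippage in recruitment, with December 2027 kept, would widen the gap.

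**Conclusion.** The contradiction is certain and needs no assumption: about 9 months are allowed where the article's own windows need 16 and 17. The date is wrong as written, and the primary outcome depends on it, so it should be corrected.

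The consequences are conditional. If data were closed or analysed in December 2027, about 179 women (15%) would lack the full window and about 6–9% of live births would fall after the cut, given uniform accrual, the two conception patterns and 38 weeks to birth. The shrinkage to about 27% versus 36%, and the loss of 3 to 4.6 points of power, need the further step that those pregnancies are scored as failures. The article does not state that step. The endpoint, its window and the sample size stand, and nothing here points to bias in favour of either arm.

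**What to change.** Reconcile the Trial status paragraph with the Week 26, Primary outcome and Secondary outcomes sections. Restate the expected end of follow-up as about July 2028 for live birth and about August 2028 for pregnancy complications, or as the date on which the last ongoing pregnancy has ended, if earlier. State that no primary analysis will be run before then. If recruitment slips, move these dates with it.

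The cost is a completion date 7–8 months later, with funding and staff to match. The extra work is low-intensity follow-up of women already pregnant, which the Week 26 section already requires. Sample size, outcomes and visits do not change.
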